#### Handling of missing values

Since the sample size estimations take into account the drop-outs during the study, sufficient data should be obtained.

The primary analysis of data will be an "intention to treat" analysis (with only actual values presented) and will include only subjects having completed the study. We will also perform sensitivity analyses by examining different models of missing data and describe the range of possible outcomes based on the various models. For example, we will perform a "baseline carried forward" analysis and a "last observation carried forward" analysis as part of the sensitivity analysis.

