## Subjects

Families where both parents are < 65 years old, and where at least one parent is obese (BMI>30 kg/m^2) and the other is overweight (BMI>28 kg/m^2) will be offered inclusion in the study with the aim of losing weight and maintaining the weight loss. Families will have 1-3 children, and at least one child aged between 5 and 18 years will be overweight (defined according to Cole *et al.* (2), i.e. with an iso-BMI>25). A total of 150 adult subjects plus children (75 families) will be screened and approximately 135 adults are expected to be included in the initial weight loss phase of the study, with the aim of having a total of 110 subjects for the subsequent randomization to the 5 dietary

arms. This number will provide an anticipated completion of more than 80 subjects at the 12-month visit.

Subjects will be recruited through the department's waiting list, local press or via referrals from local general practices or from other medical departments. Radio/television or newspaper advertising may also be employed if necessary. Eligible subjects will only be included after they have been informed about the study and signed informed consent forms (including children, see Section 11).

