## **6. STUDY TIME SCHEDULE**

The study is planned to initiate recruitment of families by September 2005 and to be started in January 2006 (LCD diet), with a staggering period of about 12 weeks. The inclusion into the randomized period will start around March, 2006 and stop around June 1, 2006. The active 12 months intervention period will be finished at around June 1, 2007 and the final 24-month follow up visit will complete the study around June 2008. Subsequent analysis, data handling and writing of publications will be performed in years 2008-2010.

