### 8.2.2 MAIN OUTCOME MEASURES

The main outcome measures in this study for adults are body weight loss maintained (kg), changes in body composition (DEXA/bioimpedance), proportion of subjects maintaining > 0, 5 and 10% of initial weight loss, and drop-out rate. Main outcome measures for children are changes in the proportion of overweight and obese children at 6 and 12 mo, and changes in age-associated BMI, % whole body fat and drop-out rate.

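### The primary analysis is labelled intention to treat but is restricted to subjects who completed the study, and completion is not defined, although drop-out is itself a main outcome

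*Protocol*

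**What the plan says.** Section 8.2.4, under Handling of missing values, sets the primary analysis in one sentence. It begins "The primary analysis of data will be an 'intention to treat' analysis (with only actual values presented" and goes on to say that the analysis "will include only subjects having completed the study". As sensitivity work the protocol promises a range of missing-data models, and as examples "we will perform a 'baseline carried forward' analysis and a 'last observation carried forward' analysis".

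Other places that bear on this:

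- Section 8.2.2 lists among the adult main outcomes "proportion of subjects maintaining > 0, 5 and 10% of initial weight loss, and drop-out rate", and among the children's "changes in age-associated BMI, % whole body fat and drop-out rate". The Synopsis also lists drop-out as primary for adults. Section 8.2.5 compares time to withdrawal by Kaplan-Meier plot and log-rank test.
- The Synopsis (Subjects) aims to randomise 110 adults and adds: "This number will provide an anticipated completion of more than 80 subjects at the 12-month visit".
- Section 6 says "the final 24-month follow up visit will complete the study around June 2008".
- Section 5.3 removes subjects withdrawn for severe protocol violations from the analysis. Section 8.2 leaves decisions on excluding subjects or values to the investigator.
- Section 8.2.7 sizes the trial on weight change to week 26, with a 1.0 kg difference and an SD of 2.5 kg.

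**The concern.** An analysis limited to completers is not intention to treat, so the sentence contradicts itself, and an analyst who follows it will select subjects on something that happens after randomisation. The protocol treats drop-out as a result that diet may influence, and then conditions the weight comparison on it. The proportions maintaining weight loss would also lose drop-outs from their denominator.

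Different drop-out is easy to imagine for control against the rest: under section 3 the control families pay for their own food and get no advice on composition, while the other four groups shop free of charge. The trial is also open-label (section 4.3).

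Because completion is undefined, the rule can also make the week-26 result depend on what happens after week 26. At stake is the protection that randomisation gives to the main weight comparison.

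**Working it through.** **1. The text.** The two halves of the sentence name different populations: all randomised subjects (the label) and completers (the rule). The limit to actual values only rules out imputation. It does not require dropping a subject who has an actual week-26 value but no later one. The completer clause does that.

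**2. What completion could mean.**

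| Reading | Effect on the week-26 comparison |
|---|---|
| Week 26 reached | Only losses before week 26 are removed |
| Week 52 reached | Subjects with a week-26 weight who leave between weeks 26 and 52 are also removed |
| Week 104 reached (section 6 has the study end there) | Anyone who leaves before week 104 is removed, whatever was measured at week 26 |

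**3. Loss the protocol expects.** From 110 randomised and more than 80 completing 12 months: (110 − 80)/110 = 27.3%. This is a ceiling for month 12. The protocol gives no figure for week 26 or week 104.

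**4. Data the primary analysis would ignore for non-completers.** Section 7.1.1 records adult weight at visits 10 to 17, eight visits between randomisation and week 26. Sections 5.3 and 7.1.1.20 also ask for a weight at discontinuation.

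**5. Size of the possible bias.** In one arm let d be the fraction lost and E the mean regain of drop-outs minus that of completers. The mean over everyone randomised is the completer mean + d × E, so the completer mean is too low by d × E. With the same E in both arms:

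bias in the difference = (difference in d) × E

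- 0.10 × 2 kg = 0.2 kg, or 20% of the 1.0 kg planning effect
- 0.10 × 3 kg = 0.3 kg, or 30%

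The 10 points and the 2 to 3 kg are assumptions. To judge them, take a normal selection model with SD 2.5 kg, drop-out probability 0.273 and correlation ρ between the tendency to drop out and weight change. Then E = ρ × 2.5 × φ(0.605)/(0.273 × 0.727) = ρ × 2.5 × 0.332/0.198, or about 4.2ρ kg. An excess of 2 to 3 kg thus needs ρ of about 0.5 to 0.7. At ρ = 0.25, E is about 1.05 kg and the bias for 10 points is about 0.1 kg.

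**6. Effect on false positives.** Use the same model with no true difference and 125 randomised per arm. The completer mean shifts by −ρ × 2.5 × φ(c)/r, where r is retention and c = Φ⁻¹(r).

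- Retention 80% v 65% (average loss 27.5%, about the ceiling): φ(c)/r is 0.350 v 0.570, so the false difference is ρ × 2.5 × 0.220. For ρ from 0.25 to 0.75 this is 0.14 to 0.41 kg. With standard error 2.5 × √(1/100 + 1/81.25) = 0.37 kg, the two-sided 5% test rejects 7% to 20% of the time.
- Equal retention of 73% in both arms: no bias under this model.

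**The case against.** The best defence is that the protocol does not stop at the completer analysis. It commits to examining several missing-data models and describing the range of results, and it tests time to withdrawal, so unequal drop-out would be seen. An unseen SAP could add detail. It also says that the sample size allows for drop-outs. All of this is fair as far as it goes, but sensitivity analyses do not change what the primary analysis is, a log-rank test detects unequal drop-out without correcting for it, and extra subjects protect power, not against bias. An SAP should not have to reverse a population that the protocol fixes.

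The defence does stand against several stronger readings that a reader might infer:

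- *That the named sensitivity analyses necessarily favour the arm with more drop-out.* The protocol does not say which baseline is carried forward. CID 2 is the adult covariate in section 8.2.4, but section 7.1.1.2 calls CID 1 the baseline examination. Carrying CID 2 weight forward sets regain to zero in drop-outs; carrying CID 1 weight forward imputes full regain. Section 3 also allows further weight loss in both periods, and where completers keep losing, carrying CID 2 weight forward penalises the arm with more drop-out.
- *That interim weights are never used, or that better methods are excluded.* The last-observation analysis uses those weights, and the two named methods are only examples.
- *That the bias would reach half the planning effect.* At 10 points this needs a 5 kg excess, above the roughly 4.2 kg maximum (ρ = 1) in step 5. Losses such as 25% v 43% average 34%, above the protocol's own ceiling.
- *That completer means are certain to be biased.* Nothing in the protocol shows that people who regain tend to leave, and the free-food difference separates control from groups 1 to 4, not those four from one another.

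**Conclusion.** The point holds on the text alone. The primary analysis is a completer analysis under an intention-to-treat label, completion is undefined, and on one natural reading the week-26 comparison depends on attendance up to week 104. No other section cures this, and sections 5.3 and 8.2 widen it by allowing further exclusions after randomisation.

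The bias is a risk, not an established fact. It arises when drop-out is related to weight change and differs by arm. With up to about 27% of adults lost by month 12, plausible inputs give 0.2 to 0.3 kg against 1.0 kg, and about 0.1 kg if the link between drop-out and regain is weak. These sizes rest on assumed drop-out differences, an assumed excess regain or correlation, and an SD of 2.5 kg. The protocol supplies only the SD and the ceiling on loss. The sentence should be corrected before any outcome data are analysed.

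**What to change.** Replace the sentence in section 8.2.4 with a statement that:

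- the primary analysis includes all randomised subjects, adults and children, in the group assigned;
- it uses all observed post-randomisation weights (for children, with the heights taken at the same visits), for example in a mixed model for repeated measures adjusting for the CID 2 value in adults or the CID 1 value in children;
- the completer analysis is supportive, with completion defined by a named visit.

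Bring the exclusions in sections 5.3 and 8.2 into line, so that withdrawal for a protocol violation or an investigator's decision does not remove a randomised subject from the primary analysis.

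State which baseline is carried forward. Add a sensitivity analysis in which adult drop-outs regain toward their CID 1 weight over a range of amounts.

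The cost is a change of wording and somewhat more analysis work; the weights are already scheduled. There are two drawbacks. The primary model would rely on data being missing at random, which the regain-based analysis is there to probe. Also, under section 7.2.1 only CID weights are taken fasting and in underwear, so interim weights are less standardised.

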### 8.2.5 PRIMARY HYPOTHESIS

The following primary hypothesis can be applied:

H0: The 1o outcome (weight, etc) is equal in the intervention groups at week 26 and week 52, when controlling for the value in CID2 (adults) or CID1 (children).

vs.

H1: The 1o outcome is different in the intervention groups at week 26 and week 52, when controlling for the value in CID2 (adults) or CID1 (children).

The changes in continuously distributed variables from baseline to week 26 and week 52 within treatment groups will be tested with the paired t-test or the Wilcoxon-Signed-rank test, depending on distribution (all tests two-sided).

All categorical variables will be expressed in contingency tables and analyzed using Fisher's exact test. Survival analysis using the Kaplan-Meier plot and the log-rank test will be used to investigate time to subject withdrawal.

All null hypotheses comparing groups assume equality between the treatment groups while the alternative hypotheses assume that there is a difference (two-sided). All within-group null hypotheses assume no change from baseline to week 26 or week 52 while the alternative hypotheses assume that there is a change (two-sided).

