## Aims

The main objective of the DiOGenes study is to identify the efficacy of particular diets for protection against weight gain and weight regain, in a susceptible population of obese and overweight individuals and their children. The overall study comprises a 6 to 12 months dietary intervention study in 350 families in 8 European countries (Denmark, the Netherlands, UK, Germany, Spain, Greece, Bulgaria and the Czech Republic), investigating the effect of different dietary components (high/normal protein and high/low GI) on maintenance of weight loss and prevention of weight (re)gain. In Denmark/Netherlands the study will be carried out over 12 months, in about 50 families. The responsiveness of the families to different dietary compositions and effects on body weight control and obesity related risk factors will be assessed during the dietary intervention study, with specific focus on changes in body weight and composition, appetite measures, adipose tissue gene expression and risk factors for cardiovascular disease (CVD) and type-2 diabetes. The role of genetic, environmental, social and cultural factors as well as their interactions with the studied diets on body weight control or development of obesity will also be investigated.

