### **8.2 STATISTICAL PROCEDURES**

All statistical analysis described in this protocol will be performed by the investigator. All analysis and tabulations will be performed using the latest release of the SAS® or SPSS software or similar statistical software. Appropriate descriptive statistics will be presented for each variable; n=number of patients, mean, median, SD and min-max for continuously distributed variables, and rates and percentages for categorical variables. Statistical tests will be performed using 5% as the nominal level of significance and interval estimates will be constructed using 95% as the level of confidence. Statistical and analytical methods, and sample size considerations are discussed in the following sections. The investigator will make the decisions regarding subjects, or individual values belonging to a patient, to be excluded from the analysis. Subjects will only be excluded from the efficacy analysis when the uses of these are considered a protocol violation, putting the scientific aspects of the trial at risk. The variables that will be statistically tested are given in the Sections concerning primary and secondary variables.

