### **8.2.7 SAMPLE SIZE ESTIMATION**

The primary aim of the study is to investigate the long-term efficacy in terms of change in body weight from baseline to study end. The sample size for the proposed study was chosen to provide sufficient power to detect differences in 26-week weight regain (for primary participants) due to the effects of the different diets. The sample estimation is based on the difference between the intervention and control groups regarding weight change (kg) from baseline to week 26. In the null hypothesis we assume that the interventions groups 1 - 4 are of equal weight at week 26 compared to baseline, while the alternative hypothesis assumes that there exists a difference in weight between the treatment groups. By this covariate method we are able to test the change from baseline to week 26 while controlling for between-group differences in the baseline value.

It is anticipated that weight differences will be smallest between the low vs. high GI diets compared to the low protein vs. high protein diets. Hence the sample size has been calculated on the basis of a previous intervention study on GI (18), which found a non-significant difference in body weight change of 0.6 kg between groups using the unpaired t-test. We assume a 0.4 kg higher weight loss based on 6-month treatment, compared to the 10-week previous intervention study (18). Thus we consider that a weight loss difference of 1 kg is a clinically relevant weight loss and a priori we assume a SD of 2.01 kg.

When assuming a difference between control and intervention group of 1.0 kg (SD 2.5 kg), at least 80% statistical power and a significance level of 5%, N=125 participants per group are required (unpaired t-test). In this model, any effect size above 0.72 kg gives a power of more than 80%.

As most other studied variables in the study are secondary objectives and because the outcome of most of these variables are not easily comparable to previous studies due to the novel design of the study, there are no calculations on sample size for variables other than the primary efficacy parameter, which is weight change to week 26.

Thus, in terms of final outcome, it is accepted that post-hoc analysis will identify that not all measures of other primary or secondary outcomes will necessarily have had the appropriate sample size.

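### Week 52 is written into the primary hypothesis, but only week 26 is sized and named as the primary time point, and the planned 125 per group cannot be available at week 52

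*Protocol*

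**What the plan says.** - **Primary test.** Protocol 8.2.4 applies the ANCOVA for the primary objectives at weeks 26 and 52. Under 8.2.5 the alternative hypothesis is that the primary outcome "outcome is different in the intervention groups at week 26 and week 52"; the null hypothesis names the same two times.
- **Aim.** Section 8.2.7 begins: "The primary aim of the study is to investigate the long-term efficacy in terms of change in body weight from baseline to study end". It does not say which visit is the study end. The Synopsis (Duration of the study) and section 6 say that the 24-month follow-up visit completes the study, and 8.2.1 lists weeks 26, 52 and 104.
- **Sizing.** The same section calculates 125 participants per group for a 1.0 kg difference at week 26. It then says that nothing else was sized, apart from "the primary efficacy parameter, which is weight change to week 26".
- **Concession.** The last sentence of 8.2.7 accepts, in general terms, that other primary or secondary outcomes may turn out not to have had an adequate sample size.
- **Who reaches 12 months.** Synopsis, Aims: "In Denmark/Netherlands the study will be carried out over 12 months, in about 50 families". The whole study is 350 families in eight countries over 6 to 12 months.
- **Numbers here.** Synopsis, Subjects: 110 adults are to be randomised to five arms. "This number will provide an anticipated completion of more than 80 subjects at the 12-month visit".
- **Analysis set.** Under 8.2.4 (Handling of missing values) the primary analysis includes completers only.

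**The concern.** A reader cannot tell from the protocol whether the trial's primary claim concerns week 26, week 52, both, or the end of the study. Sections 8.2.4 and 8.2.5 give weeks 26 and 52 equal standing, while 8.2.7 gives primary standing to week 26 alone.

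The difference has practical consequences. The sizing is expressed per group, and six of the eight countries have no 12-month intervention, so pooling centres cannot supply the planned number at week 52. As written, a non-significant week-52 comparison counts against the primary hypothesis, although the protocol states no power for it. It could be taken as evidence that the diets have no long-term effect when the comparison may simply have been too small to show the 1.0 kg that 8.2.7 calls clinically relevant.

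**Working it through.** **Inputs.** Two-sided 5% level (8.2 and 8.2.5). Difference 1.0 kg, with SD 2.5 kg in the calculation sentence and 2.01 kg in the a priori sentence (8.2.7). Five arms of about equal size (4.2). 110 adults randomised and just over 80 expected at 12 months (Synopsis, Subjects).

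**Step 1: the plan's own week-26 figure.** n per group = 2(1.960 + 0.842)² × SD² / difference².
- SD 2.5: 2 × 7.849 × 6.25 = 98.1, so 99; the exact t-test needs 100.
- SD 2.01: 2 × 7.849 × 4.04 = 63.4, so 64; the exact t-test needs 65.

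The stated 125 equals 100 / (1 - 0.20), that is, with 20% drop-out, a rate the protocol does not give. This is a separate matter. At 125 per group the week-26 comparison has 88% power (SD 2.5) or 97% (SD 2.01), so week 26 is adequately sized if the full study delivers that number.

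**Step 2: numbers per arm at week 52.**
- Expected completers: 80 / 5 = 16.
- Everyone randomised, with no loss: 110 / 5 = 22.
- A second country of equal size (assumption): 2 × 16 = 32 completers, or 2 × 22 = 44 with no loss.

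The Aims sentence can also be read as about 50 families across both countries together. With at most two parents each, that is 100 / 5 = 20 adults per arm, inside the 16-22 range. On no reading does the number approach 125.

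**Step 3: pairwise power at week 52.** Noncentral t with df = 2n - 2 and noncentrality 1.0 / (SD × √(2/n)). For n = 16 and SD 2.5: 1.0 / (2.5 × √0.125) = 1.13, df 30, critical value 2.04, power 19%.

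| n per arm | Basis | Power, SD 2.5 / 2.01 | Difference detectable with 80% power (kg), SD 2.5 / 2.01 |
|---|---|---|---|
| 16 | protocol, completers | 19% / 28% | 2.56 / 2.06 |
| 22 | protocol, no loss | 25% / 36% | 2.16 / 1.74 |
| 32 | equal second country, completers | 35% / 50% | 1.78 / 1.43 |
| 44 | equal second country, no loss | 46% / 64% | 1.51 / 1.21 |

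**Step 4: pooled contrasts.** A protein or GI main effect sets two arms against two:
- One country, completers, 32 v 32: 35% / 50%.
- Two equal countries, completers, 64 v 64: 61% / 80%.
- Two equal countries, no loss, 88 v 88: 75% / 91%.

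**The case against.** **The plan already concedes the point.** Section 8.2.7 names one primary efficacy parameter and accepts that other primary outcomes may be undersized. This stands in part: the sponsor did not claim that everything is powered. But the sentence is general. It does not mention week 52, does not take it out of the hypotheses in 8.2.5, and does not settle what the study end is.

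**Pairwise power is the harshest view.** The 1.0 kg comes from a low- versus high-GI comparison, and four of the arms form a 2x2 layout. Pooled contrasts do better, as Step 4 shows. A reader might infer that every week-52 comparison falls well short of 80%; the documents do not support that, because with two equal countries some pooled contrasts reach or pass it. Pairwise is nevertheless how the 125 per group is framed, and on this centre's completers alone the pooled contrast still has only 35-50%.

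**The inputs are borrowed.** No week-52 effect, SD or Dutch enrolment is given. Section 8.2.7 itself assumes that the difference grows from 0.6 kg at 10 weeks to 1.0 kg at 6 months, so holding 1.0 kg at 12 months is not the plan's assumption; the SD may also change. This stands, and the power figures are illustrative only.

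**Two further inferences fail.** A reader might take the study end to mean week 52, but the protocol's own schedule ends at the 24-month visit. A reader might also take the hypothesis to require success at both times, so that week 52 limits the whole primary claim; the protocol states no such rule.

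**Conclusion.** The concern holds in limited form. Sections 8.2.4, 8.2.5 and 8.2.7 disagree on the primary time point, and the week-52 primary comparison has no sizing. That conclusion needs no assumption. That 125 per group is unavailable at week 52 follows from the restriction of the 12-month study to two countries.

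The size of the shortfall is less certain. On the protocol's own counts, a pairwise 1.0 kg comparison has about 19-36% power. If an equal second country is assumed, the pairwise range is 35-64%, and pooled protein or GI contrasts have 61-80% with expected completers or 75-91% with no drop-out. All of these hold the 1.0 kg effect fixed and reuse the week-26 SDs. They ignore clustering of parents within families and multiple comparisons, both of which could lower power. Week 26 is not called into question.

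**What to change.** 1. In 8.2.4 and 8.2.5, restrict the adult primary hypothesis to weight change from CID2 to week 26, the time point that 8.2.7 already sizes and names.
2. In the opening aim of 8.2.7, replace the study end with week 26.
3. Make week 52 a secondary comparison in the centres that continue to 12 months, reported as an estimate with a 95% CI.
4. In 8.2.7, state the expected week-52 number per group and the detectable difference, labelled as pairwise (about 1.7-2.6 kg at 16-22 per arm, on the plan's SDs). Add that a non-significant week-52 result is not evidence of no long-term effect.

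Keeping week 52 as a separately labelled endpoint with its detectable difference stated would also remove the inconsistency. Demotion is the simpler choice, because it matches what 8.2.7 already says.

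The cost is protocol wording, with no extra participants or visits. The 12-month result loses primary status, and a less favourable detectable difference is printed for it.

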### 8.2.4 STATISTICAL METHODS FOR THE PRIMARY OBJECTIVES

Analysis of Covariance (ANACOVA) will be used to compare the main outcome measures in the intervention groups at week 26 and week 52 using the data from CID2 (after weight-loss, adults) or CID1 (children) as covariate.

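### For the weight-loss-maintenance and children's overweight proportions, Fisher's exact test does not match a primary hypothesis that controls for the starting value

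*Protocol*

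**What the plan says.** Protocol 8.2.4 gives one method for all main outcomes: "Analysis of Covariance (ANACOVA) will be used to compare the main outcome measures in the intervention groups at week 26 and week 52". The covariate is the CID 2 value for adults and the CID 1 value for children. Section 8.2.5 frames the null and alternative hypotheses in the same way, "when controlling for the value in CID2 (adults) or CID1 (children").

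Section 8.2.2 includes binary measures among those main outcomes. For adults they are "proportion of subjects maintaining > 0, 5 and 10% of initial weight loss, and drop-out rate"; for children, "changes in the proportion of overweight and obese children at 6 and 12 mo", and again drop-out.

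Later in 8.2.5 comes the rule for such measures: "All categorical variables will be expressed in contingency tables and analyzed using Fisher's exact test". Withdrawal gets a second analysis: "Survival analysis using the Kaplan-Meier plot and the log-rank test will be used to investigate time to subject withdrawal". Section 8.2 sets the level: "Statistical tests will be performed using 5% as the nominal level of significance".

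**The concern.** Two adjoining sections name different methods for the same outcomes. ANACOVA as written in 8.2.4 covers every main outcome but is a method for continuous data. The rule written for categorical data, in 8.2.5, drops the covariate that the hypothesis is built on.

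The covariate matters here. Whether an adult is beyond a given percentage loss at week 26 depends heavily on how much that adult had lost by CID 2. A child's overweight status later is likewise expected to depend on BMI at CID 1. An unadjusted table treats this known variation as noise. At stake are the precision of several declared main outcomes and a clear statement of which analysis counts. A reader of the results could not tell whether an adjusted or an unadjusted comparison had been planned.

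**Working it through.** **The plan's own figure.** Section 8.2.7 gives no event rate, baseline correlation or power for any categorical outcome, so there is no figure of that kind to reproduce. Its sample size concerns mean weight change: n = 2(1.96 + 0.842)² × 2.5² / 1.0² = 98.1, so 99 per group. The stated 125 per group gives about 88% power. I take 125 per group, 1.0 kg and SD 2.5 kg from there; 8.2.7 also gives an SD of 2.01 kg.

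**Assumptions not in the protocol.** Start weight 100 kg (SD 15), LCD loss 11% (SD 3), mean regain 1 kg, independent subjects. The outcome is more than 10% of CID 1 body weight lost at week 26, the reading closer to the Synopsis.

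**Why adjustment matters, by hand.** Loss at week 26 is LCD loss minus later change. At 100 kg, 2.5 kg is 2.5 percentage points.
- SD of the outcome: √(3² + 2.5²) = 3.91 points. Correlation with loss at CID 2: 3/3.91 = 0.77.
- A 1-point effect is 1/2.5 = 0.40 SD given the CID 2 loss, but only 1/3.91 = 0.26 SD without it.
- Control mean is 11 − 1 = 10%, so control responders are 50%; with the effect, Φ(0.256) = 60.1%.
- Unadjusted z = 0.101/√(0.5×0.5/125 + 0.601×0.399/125) = 1.61. Power ≈ Φ(1.61 − 1.96) = 36%.

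Simulation agrees: 37% for an unadjusted likelihood-ratio test, 31 to 32% for Fisher, 54 to 56% for logistic regression on diet and % loss at CID 2. So 5 to 6 of the roughly 24 points are Fisher's conservatism and the rest is non-adjustment.

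**Sensitivity** (simulated power, 125 per group, 1 kg effect, >10% cut-off unless stated):

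| Scenario | Fisher | Adjusted logistic | Gap (points) |
|---|---|---|---|
| SD 2.5 kg, LCD-loss SD 3 | 32% | 56% | 24 |
| LCD-loss SD 2 | 44% | 62% | 18 |
| LCD-loss SD 4 | 23% | 48% | 25 |
| Weight-change SD 2.01 kg | 36% | 68% | 32 |
| Weight-change SD 5 kg | 15% | 22% | 7 (6 to 8 over repeat runs) |
| Every adult's LCD loss at least 8% | 42% | 59% | 17 |
| >5% cut-off (89% control responders) | 16% | 32% | 16 (14 in a repeat) |
| No effect | 4.7% | 4.6% | – |

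**A check free of the weight model.** Dichotomise a normal outcome with a total standardised effect of 0.4 and 50% control responders, varying only the baseline–outcome correlation (125 per group):

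| Correlation | Fisher | Pearson chi-square | Adjusted logistic |
|---|---|---|---|
| 0 | 64% | 68% | 69% |
| 0.3 | 66% | 70% | 73% |
| 0.5 | 66% | 71% | 77% |
| 0.7 | 65% | 70% | 87% |
| 0.9 | 66% | 71% | 97% |

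The Fisher column is higher than above because 0.4 is here applied to the whole outcome. The gap is about 5 to 7 points up to a correlation of 0.3, 11 at 0.5, and above 20 only from about 0.7.

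**Ceiling.** Read literally, 8.2.2 asks whether more than 10% of the initial loss is retained. Under the base assumptions that holds for 99.1% and 99.6% of the two groups, and power is 0% with Fisher and about 10% with logistic regression. Changing the test does not rescue that outcome.

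**The case against.** The case against giving this much weight is substantial.

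- **Validity is not at stake.** Under randomisation, no diet effect given the starting value implies equal proportions overall, so Fisher's test keeps its level against the stated null. This stands.
- **The main analysis is elsewhere.** Section 8.2.7 names weight change to week 26 as the primary efficacy parameter, analysed with the CID 2 covariate, and concedes that other primary outcomes may be under-sized. A reader might infer that the trial will miss a diet effect of its target size. That does not follow: the proportions are cut-offs of the same weights, and the weight analysis has about 88% power at 125 per group. Conceding a limited sample size is still no reason to drop a covariate that the hypothesis names.
- **The size rests on assumptions.** A reader might infer that power is always cut sharply. The protocol gives no figures that establish this; the gap runs from a few points to more than 20.
- **Not every categorical main outcome is affected.** Drop-out has no starting value to control for and also gets a log-rank test.
- **Small arms.** With about 11 families per diet (4.2), hence up to 22 parents, simulated power was 6% with Fisher against 15% with logistic regression. This comparison is unsafe: the unpenalised logistic test rejected roughly 7 to 12% of the time with no effect. I place no weight on it.
- **Could the SAP settle it?** Model detail may be left there, but the protocol itself fixes both the hypothesis and the test, and they disagree.

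**Conclusion.** The mismatch is in the text and holds for two sets of outcomes: the adult maintenance proportions and the children's overweight/obese proportion. For these, the named test ignores the starting value that 8.2.4 and 8.2.5 say will be controlled for, and precision is lost. At 125 per group with a 1 kg effect and the 10%-of-body-weight cut-off, the loss is about 24 points of power with a weight-change SD of 2.5 kg, falling to about 6 to 8 points at 5 kg, with Fisher's conservatism included. These figures rest on the assumed LCD loss, start weight and regain, and ignore clustering within families. No calculation supports a figure for the children's outcome. The point is worth correcting because the change is nearly free, but it does not threaten the trial's main conclusion on weight.

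**What to change.** - In 8.2.4, limit the ANACOVA sentence to continuous outcomes.
- In 8.2.5, name logistic regression for the adult maintenance proportions and the children's overweight/obese proportion, with diet group and the starting value as terms: % weight lost from CID 1 to CID 2 for adults, CID 1 age-adjusted BMI for children.
- Use Firth's penalised likelihood in small arms or with sparse cells.
- Report standardised risk differences with 95% confidence intervals, so that the result is on the scale of the proportions themselves.
- Keep Fisher's test for near-empty tables and for variables with no baseline value, such as drop-out.
- Reconcile the maintenance outcome between the Synopsis (percentage weight loss) and 8.2.2 (percentage of the initial loss). The choice decides whether the outcome is informative or at a ceiling.

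The cost is wording only, since the CID 1 and CID 2 measurements are already scheduled (7.1.1.2, 7.1.1.7, 7.1.2.2). The downside is that a model replaces an exact test, and that small arms need penalisation.
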